## Abstract

**Background:**

Although considerable evidence exists about the effectiveness of audit coupled with feedback, very few audit-with-feedback interventions have been done in either home care or supportive living settings to date. With little history of audit and feedback in home care or supportive living there is potential for greater effects, at least initially. This study extends the work of an earlier study designed to assess the effects of an audit-with-feedback intervention. It will be delivered quarterly over a one-year period in seven home care offices and 11 supportive living sites. The research questions are the same as in the first study but in a different environment. They are as follows:

1. What effects do feedback reports have on processes and outcomes over time?

2. How do different provider groups in home care and supportive living sites respond to feedback reports based on quality indicator data?

**Methods:**

The research team conducting this study includes researchers and decision makers in continuing care in the province of Alberta, Canada. The intervention consists of quarterly feedback reports in 19 home care offices and supportive living sites across Alberta. Data for the feedback reports are based on the Resident Assessment Instrument Home Care tool, a standardized instrument mandated for use in home care and supportive living environments throughout Alberta. The feedback reports consist of one page, printed front and back, presenting both graphic and textual information. Reports are delivered to all employees working in each site. The primary evaluation uses a controlled interrupted time-series design, both adjusted and unadjusted for covariates. The concurrent process evaluation includes observation, focus groups, and self-reports to assess uptake of the feedback reports. The project described in this protocol follows a similar intervention conducted in our previous study, Data for Improvement and Clinical Excellence--Long-Term Care. We will offer dissemination strategies and spread of the feedback report approach in several ways suited to various audiences and stakeholders throughout Alberta.

**Significance:**

This study will generate knowledge about the effects of an audit with feedback intervention in home care and supportive living settings. Our dissemination activities will focus on supporting sites to continue to use the Resident Assessment Instrument data in their quality improvement activities.

## Background

Although there is evidence about interventions to improve quality of care in some healthcare settings, the evidence for quality-improvement interventions in long-term care (LTC) is variable [1-7]. Specific to audit and feedback interventions, there is little evidence on utility of this type of intervention in continuing care settings. With unprecedented growth in both home care (HC) and supportive living (SL), data about the quality of care as well as about how to improve quality of care in these settings are a priority. Subsequently, we did a study on an audit-with-feedback intervention across the three streams of continuing care: LTC, HC, and SL. The protocol we report in this paper is on the second phase of our study that will be carried out in HC and SL. The study protocol for the first phase in LTC was previously reported [1]. In this second phase, we expand the original protocol to cover HC and SL settings.

The number of healthcare resources needed to meet the needs of the large and ever-growing HC and SL sector populations is a top priority of healthcare organizations today. HC is defined as an array of services designed to meet individual and family needs [8,9]. SL is continuing care, usually in congregate living settings, and is also referred to as assisted living or designated assisted living in some sectors. The services vary from setting to setting to a degree but are primarily home care and support services to seniors. The Canadian Home Care Association reported that from 1995 to 2006, the number of publicly funded HC clients grew by nearly 100% to approximately one million clients at any given time [9-12]. Further, the Health Council of Canada reported that from 1995 to 2002, the number of Canadians receiving publicly funded HC increased by 60%. The need to deliver quality care to this growing population is essential and must be done in an efficient and effective manner in order to maximize our limited healthcare resources [9,11]. In the Government of Alberta's strategy, Aging in the Right Place, various initiatives are outlined to address the increasing healthcare needs of HC and SL clients [13]. The strategies contained within Aging in the Right Place involve enhancing HC and SL through improved assessment, expansion of current programs, introduction of appropriate emergency supports, and facilitation of transitions from acute care back into the community [13]. One outcome is that people receive the right care at the right time by the right provider. These actions are further supported in the Alberta Continuing Care Association document on implementing recommendations of the Ministry Advisory Committee on Health (MACH) [14,15]. Within the MACH report, there is an emphasis on incorporating the pillars of acceptability, accessibility, appropriateness, effectiveness, efficiency, and safety through the use of evidence-based research into SL facilities [14]. In order to mobilize an effective healthcare workforce, it is essential that evidence-based practice be at the forefront to ensure a high quality of care for HC and SL clients. In order to adequately attain a relevant and meaningful level of knowledge among community healthcare providers, HC and SL client assessment data must be incorporated into research-based knowledge-translation (KT) strategies [16]. We position quality-improvement initiatives, such as audit and feedback, as a KT strategy.

Despite the aforementioned literature, there is a dearth of evidence from HC and SL settings as these sectors have received relatively little attention in terms of implementation of evidence-based practice, or at least little that is reported in the literature. Further, very little research has been done to examine the utility of client assessment data on improving nursing care in the HC and SL sectors. The Resident Assessment Instrument-Home Care (RAI-HC) tool belongs to a suite of tools used by organizations to collect, analyze, and understand the health status of clients. The RAI tools help to standardize client assessment and form an evidence base to influence clinical practice and policy decisions and thus have been mandated by many organizations [17]. Within community settings, such as HC and SL, the RAI-HC is a useful tool for highlighting themes related to functioning and quality of life of clients [18]. The RAI-HC quality indicators can be assessed and recorded and include categories such as pain, falls, or depression [18]. The assessment data contained within the RAI-HC is easily accessible and, therefore, can be used to assess trends or patterns in client quality indicators.

The detection of patterns and trends within a particular RAI-HC data set can be further utilized to describe areas in which quality-of-care improvements could be made through increased use of evidence-based practice. In order to increase use of evidence-based practice and subsequently improve care in HC and SL, the relationships between the assessment findings and their usefulness and applicability, including how well they are understood by healthcare providers, must be explored; one way to do this is through the use of audit and feedback as a quality-improvement strategy.

### Primary purpose and study objectives

The primary purpose of the Data for Improvement and Clinical Excellence (DICE) project is to assess the effects of an audit with feedback intervention in all three streams of continuing care: LTC, HC, and SL. The LTC intervention has been recently completed and is in the monitoring phase [1]. The HC and SL audit-with-feedback intervention will be delivered quarterly over a one-year period in seven HC offices and 11 SL sites across Alberta, using data from the RAI-HC.

We address these research questions:

1. What effects do RAI feedback reports have on processes and outcomes over time?

2. How do different provider groups in HC and SL respond to feedback reports based on RAI-HC quality indicator data?

## Methods

The overall intervention evaluation uses a controlled interrupted time-series design with quarterly feedback reports in the seven HC offices and 11 SL sites across Alberta. Follow-up surveys to assess uptake of the audit-with-feedback intervention will be offered to all participating employees one week after feedback report distribution. The purpose of the follow-up survey is to assess staff response to the feedback reports and their intent to change their behavior based on what they learned from the feedback. We will not be measuring actual change in behavior through the surveys but rather their *intent *to change their behavior. This is similar to the survey tool that was used in the Data for Improvement and Clinical Excellence--Long-Term Care (DICE-LTC) study, with only wording revised to suit the HC/SL environment. A sample survey instrument can be found in Additional File 1.

We will use in-person audit and feedback in two zones and electronic distribution in two zones. This will be more fully described later in this protocol paper.

The process evaluation will be conducted concurrently with the prospectively collected survey data and will consist of observation, focus groups, and self-report measures to assess uptake of the feedback reports. We define uptake as reading the feedback reports, discussing with colleagues and managers, and reporting some degree of intention to change behavior based on the reports. Observation will occur in the sites where we deliver the feedback reports in person. The focus groups will be targeted sessions based on the findings of the observations and the self-report survey and will be held in four of the participating sites.

We received ethics approval from the University of Alberta Health Research Ethics Board, panel B. We obtained operational approval for all sites from all participating study organizations. Participation by staff is voluntary and will not affect their employment in any way.

### Project team

The project team comprised both researchers and decision makers who had existing relationships prior to this project, primarily through the Knowledge Brokering Group (KBG). The KBG team was focused on using data to inform decision making in continuing care settings. The overall makeup of the team and each member's background is described in the DICE-LTC protocol paper [1]. The specific program funding for this project requires active collaboration between researchers and decision makers [19], and the team works on a linkage and exchange, integrated KT model. New team members were added for this second phase in HC and SL, and again, the researcher lead and decision-maker partners had existing collaborative relationships. We provide an updated description of the project team for DICE-HC in Additional File 2.

### Settings and sample

The settings are seven HC offices and 11 SL sites across Alberta, Canada. The selected HC sites are part of Alberta Health Services (AHS) and their direct care providers and managers are employees of AHS, whereas the SL sites are operated by provider organizations under contract to AHS and the direct care providers and managers are employees of the provider organization. However, in all sites, case management and assessments are carried out by case managers who are part of AHS. The sites have all implemented the RAI-HC instrument [20].

### Recruitment

We recruited HC offices and SL sites in rural and urban areas across four zones in Alberta (North, Central, Calgary, and South) to participate [21]. Ideally, by the time we begin feedback reports, clients/residents of these HC office and SL sites would have been assessed using RAI-HC at least once and preferably more than once. The degree of RAI-HC implementation guided our choice of sites, as most HC and SL sites in Alberta began implementation of RAI-HC in 2007. The roll-out was staggered across the province and was fully implemented by July 2011 and, going forward, all new client assessments and re-assessments will be completed using the RAI-HC. We recruited HC offices and SL sites with at least 10 nonregulated staff, as well as at least 20 to 30 clients/residents being assessed using the RAI-HC tool in order to obtain a critical mass. We recruited direct care employees from all of the professions, disciplines, and groups in the participating sites. Participants may include site managers, case managers, registered nurses, licensed practical nurses, healthcare aides, occupational therapists and assistants, recreational therapists and assistants, physical therapists and assistants, pharmacists, and social workers.

### The intervention

#### Procedures for feedback report generation and distribution

Feedback report distribution and data collection will occur in two ways: either in person or electronically. This was done for two reasons: first, logistically given the geographic size of Alberta and the desire to include most zones and, second, to assess the difference in response and utility between in-person and electronic feedback reports. We will use the Alberta Context Tool (ACT) to assess context in the sites as we did in DICE-LTC [1,21,22]. The ACT will be administered at the beginning of the project immediately following in-person information sessions and prior to beginning report distribution. Information sessions and administration of the ACT tool during the information sessions will occur in-person for all sites across the province.

Unlike previous studies using feedback for quality improvement, this study focuses on the individual rather than the whole organization [23], and front-line staff are targeted to receive the feedback reports directly. Thus, our purpose is to provide the feedback reports, generated using RAI-HC data, directly to front-line staff using either an in-person distribution approach (North and Central zones) or via electronic distribution (Calgary and South zones). The RAI-HC covers a wide range of process and outcome data at the individual client level, and assessments are updated annually for each client unless there is a change in a client's health status or their functional or cognitive status, or if the client has been admitted to hospital. The quality indicators we have chosen to include in the feedback report are negative mood, risk of falls, pain, delirium, and visits to the hospital in the last 90 days. These five areas are the top domains identified as important by HC and SL staff. They were selected in 2010 using a voting process completed by AHS senior leadership, who consulted with their managers and/or direct care employees. The RAI-HC data will also be used to measure client-level outcomes.

Data will be extracted by AHS for each of the participating sites. All personal identifiers will be removed prior to extraction at AHS and delivery to the researchers. The data extraction for each quarter will include all assessments completed within the prior 12-month period so that in each quarterly report we will capture one year's worth of assessment data. The anonymized data will be submitted to the research team who will generate feedback reports.

The feedback reports are full color line graphs with minimal text on one double-sided page. An example of a feedback report is provided in Additional File 3. The reports will be distributed quarterly for one year. The first and third quarterly reports will include pain, negative mood, and falls. The second and last quarterly reports will also include delirium and visits to the hospital in the last 90 days. Each report will have the site's own data, with aggregate data from all other sites to compare their performance on the specific quality indicators to all other participating sites.

We will distribute feedback reports to all available employees at the participating sites once each quarter. We elected to do quarterly feedback reports rather than monthly feedback reports for two reasons. First, it is unlikely that there will be enough new or repeat assessments completed each month to yield enough data for reliable estimates. Second, based on our observations in DICE-LTC, we did not want to burden participants with monthly reports.

The following is a description of the in-person distribution approach, followed by the modifications that we will make for the sites that are participating electronically. All of our visits will be prearranged with the site champions and during a time where we are most likely to capture the most staff on-site, for example, immediately following a team meeting when all or most staff come together at the SL site or HC office. In SL sites, there is often a huge campus, or several small sites, so it is not practical to try to reach staff outside of prearranged times. It is a similar case in HC, where staff are not in a central location, except during team meetings or in-services.

Once every three months (*i.e*., every quarter), two research assistants (RAs) will hand deliver the report to all employees present and available at each site during the time he or she is there. The reports are specific to the HC or SL site, and all direct care providers and managers within these sites are targeted to receive the report that gives them information about how the clients in their site compare to the other sites in the study on the selected indicator areas. Additional copies will be left in a central location, and staff will be told that they are welcome to take one later if they would like. The RAs will stay for about one hour after distributing reports to answer any questions or take comments. One of the RAs will also passively observe what employees do with the reports after receiving them and will discretely note how many times the employees read the reports, discuss them with others, discuss with the RA, or other actions such as throwing the reports away. No names or identifying information will be noted. We will use a simple check sheet as well as write narrative notes about the specific observations. This is the basis for our field notes and will be used in conjunction with staff self-report on the post-feedback survey to obtain an estimate of report uptake. At the end of the site visit, we will also post flyers reminding staff that we will be conducting surveys the following week.

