### Analysis

Our primary analysis, using time series with and without adjustment for covariates, including site-level context data from the ACT survey, will allow us to assess change in the client outcomes that are reported in the feedback report over time. For the primary analysis for this study, we will pool the RAI-HC data from all study sites, using RAI-HC data for six months prior to the intervention, during the intervention, and for six months after the intervention. We will assess changes in trends seen before, during, and after the intervention period for the client outcomes included in the feedback reports (pain, delirium, negative mood, falls, visits to hospital within previous 90 days) and other outcomes not included in the reports (*e.g*., pressure ulcers, incontinence, and social engagement). For the purpose of the time-series analysis, the quarterly data will be converted to monthly measures of aggregate client outcomes across all sites. Predictor variables will include the intervention dose, operationalized as the proportion of staff who were observed or who self-reported reading the reports. Data for control facilities will be requested and analyzed at the end of the post-surveillance period.

Qualitative data from the focus groups and from the narrative observation notes will be coded into themes, including specific barriers and facilitators to feedback report uptake. At the site level, these findings will be used alongside the post-feedback report survey data, the client outcome data, and the findings from the ACT tool to glean additional detail around contextual differences that may explain possible variations in responses to the feedback reports across sites.

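### Delirium and hospital visits are first fed back at report 2, yet the analysis places all five fed-back outcomes around one intervention period, with no allowance for the later start or the 90-day look-back.

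*Protocol article*

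**What the plan says.** In the protocol article, the section on feedback report generation and distribution sets four reports: "The reports will be distributed quarterly for one year". Their content alternates. "The first and third quarterly reports will include pain, negative mood, and falls", and then "The second and last quarterly reports will also include delirium and visits to the hospital in the last 90 days". Pain, negative mood and falls are therefore fed back four times from report 1. Delirium and hospital visits are fed back twice, starting at report 2.

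The Analysis section uses one time frame, "using RAI-HC data for six months prior to the intervention, during the intervention, and for six months after the intervention", and one target: "We will assess changes in trends seen before, during, and after the intervention period for the client outcomes included in the feedback reports". The list that follows names all five indicators together, with the hospital indicator defined as "visits to hospital within previous 90 days". The unit is a pooled monthly series: "the quarterly data will be converted to monthly measures of aggregate client outcomes across all sites". Exposure enters as "the intervention dose, operationalized as the proportion of staff who were observed or who self-reported reading the reports". The same section treats outcomes that are not in the reports as a separate group.

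**The concern.** An interrupted time series rests on placing the interruption where exposure begins. For delirium and hospital visits, feedback on the indicator begins one quarter after the first report, but the article describes one intervention period for all five outcomes. By the Analysis section's own division, these two belong with the outcomes not in the reports during the first quarter.

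The dose variable does not repair this. A staff member who reads report 1 counts as dosed for delirium, although report 1 carries nothing on delirium.

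Hospital visits have a second delay. An assessment made shortly after report 2 mostly counts visits that happened before it.

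At stake is the reading of two of the five fed-back outcomes in the primary analysis. A real effect would look smaller, a prompt change could look gradual, and the change at the end of the intervention year could be misread as benefit fading once reports stop.

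**Working it through.** The article states no figure to reproduce here. The month counts below follow from its text plus timing assumptions; the regression figures are illustrative.

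**Inputs from the article:** quarterly reports for one year; delirium and hospital visits only in reports 2 and 4; a 90-day look-back for hospital visits; a window of 6 + 12 + 6 = 24 monthly points.

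**Assumptions:** report 1 opens the intervention period; reports fall at months 0, 3, 6 and 9; assessments are spread evenly within a month; 90 days = 3 months; the true effect is an immediate, lasting step of 1.0 at report 2, without noise.

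**Step 1, exposure by intervention month x = 1 to 12**
- Delirium: 0 in months 1-3, then 1 in months 4-12. Unexposed: 3/12 = 25%.
- Hospital visits: 0 in months 1-3. In months 4, 5 and 6 the share of the look-back lying after report 2 is 0.5/3 = 0.17, 1.5/3 = 0.50 and 2.5/3 = 0.83. It is 1 from month 7. Exposed month-equivalents: 1.5 + 6 = 7.5. Unexposed: 12 - 7.5 = 4.5, or 37.5%.
- The look-back alone would cost 1.5 month-equivalents even if hospital visits were in report 1. The one-quarter delay adds the other 3.

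**Step 2, mean during minus mean before**
- Delirium: 9/12 = 0.75 of the true step.
- Hospital visits: 7.5/12 = 0.625.

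**Step 3, three-phase segmented regression with a common break at report 1**

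The before-phase is flat at 0, so the fitted line in the 12 during-months gives the terms. The sum of squares of x is 143 and its mean is 6.5.
- Delirium: cross-product 13.5; slope 13.5/143 = 0.094 per month; level at month 1 = 0.75 - 5.5 × 0.0944 = 0.23; projection to month 13 = 0.75 + 6.5 × 0.0944 = 1.364 against a true value of 1, an apparent end drop of -0.36.
- Hospital visits: cross-product 16.42; slope 0.115; level 0.625 - 5.5 × 0.1148 = -0.01; projection 1.371, an end drop of -0.37.

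**Step 4, sensitivity to coding**
- Starting the slope counter at 1 instead of 0 gives levels of 0.23 - 0.09 = 0.14 (delirium) and -0.01 - 0.11 = -0.12 (hospital visits). The end drops become about -0.27 and -0.26.
- One break only, with data to month 24, gives levels of 0.44 and 0.23, slopes of 0.05 and 0.06, and no end-drop term.
- Range of the level term: 0.14 to 0.44 for delirium and -0.12 to 0.23 for hospital visits. The end drop, about -0.26 to -0.37, exists only in a three-phase model.

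**Step 5, outcome-specific start**
- Delirium with its break at report 2: level 1.00, slope 0.00.
- Hospital visits with a break at report 2 but no look-back allowance: level 0.49 (data to month 18) or 0.66 (to month 24). With the three transition months excluded: 1.00. A later break alone is not enough for this outcome.

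**The case against.** The strongest reply is that the article never states a common break. It gives no model equation, break coding or lag, and a fuller analysis plan, not at hand, may define these per outcome. That stands against any claim that the article specifies a faulty model. It does not remove the point: the article names five outcomes under one intervention period and defines a dose that is blind to report content, and followed as written this conflicts with its own report schedule.

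Second, estimating the effect of the whole programme from its start is a legitimate question. Staff attend information sessions and receive report 1 before report 2, so spill-over is possible. This stands. Months 1-3 are months without feedback on that indicator, not months without intervention, and they are not a clean internal control.

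Third, a sharp step is a demanding benchmark. Assessments are mostly annual, so gradual change is plausible for every outcome and a slope need not be false. This also stands, and is why the segmented figures are shown only as ranges.

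A reader might infer from a level term near zero that the effect on hospital visits would be lost. The calculation does not support that: the effect is moved into the slope, and the fitted line still averages 0.625 over the year. A reader might also infer that the primary analysis as a whole is invalid. It is not. Three of the five fed-back outcomes are untouched by the delay, and for the other two the simple contrast is attenuated toward no effect.

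**Conclusion.** The point holds as a mismatch between the report schedule and the analysis of two outcomes. On the natural reading that the intervention period starts at report 1, with reports at months 0, 3, 6 and 9, 3 of 12 intervention months for delirium precede feedback on it. For hospital visits the figure is about 4.5 month-equivalents, with full post-feedback exposure only from about month 7.

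The firmest measure of size is the during-period mean, which recovers about 75% and 62.5% of an immediate, lasting step. A common-break segmented model would shift part of the effect from level to slope, and a three-phase model could also show a spurious drop at the end of the year; how much depends on coding choices the article does not make. This should be fixed, but it does not by itself block the study.

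**What to change.** In the Analysis section, before outcome data are analysed:
- Set the interruption at report 1 for pain, negative mood and falls; at report 2 for delirium; and at report 2 followed by a 90-day transition, excluded or phased in, for hospital visits.
- Set the dose variable to zero for delirium and hospital visits until report 2.
- State that these two outcomes receive two reports, not four.
- Keep the common-start analysis as a sensitivity analysis of the whole programme.
- Do not present months 1-3 as a clean internal control.

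The cost is a change of analysis wording, with no new data. The downside is fewer exposed months in the intervention year: 9 for delirium and 6 full months for hospital visits. Fixing the break points in advance also avoids the appearance that they were chosen from the data.
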